## Measurements at Baseline and Follow-up Visits

Each patient will return to see the same physicians for follow up visits at 3, 6. 9 and 12 month after the first visit, and the following measurements will be recorded, laboratory reports will be obtained.

- Blood pressure: The subjects should be resting for at least 5 minutes prior to measurement of blood pressure. Measure the sitting or supine blood pressure, and take the mean of values of 2 continuous measurements. There should be 2 minutes interval between the 2 measurements.
- Height and body weight: Remove the shoes and socks prior to measurement, as well as wear light clothes. Formula for body mass index calculation: BMI= Body weight (kg)/Body height^2^ (m)
- Waist circumference: Remove the clothes on the waist and stand relaxed with both hands down naturally. Then use tape around the waist and adjust its location to make the tape pass the intermediate points between superior margins of hip bones at both sides and lower costal margins. Pay attention to that the tape should be parallel to the floor and cling to but no compress the skin.
- Health behavior
- Smoking history: Record the average number of cigarettes per day and smoking time. A smoker is defined as a person who smokes 1 cigarette a day on the average for at least 1 year.
- Exercise pattern: Physical inactivity means the subjects do not have frequent physical exercise (such as amount of exercise equal to that in walking for at least 20-30 minutes a day, 3-4 days a week).
- Medication: Including medication previously prescribed for glycemic control and any other concurrent medications. Record generic name, brand name, dosage, frequency, years taken, and purpose. Current and any change of medications since last recorded visit for treatment of type 2 diabetes, diabetic complications, lipid-regulation, and hypertension, including prescription drugs, OTC drugs and Chinese herbal medicines should be recorded.
- Reason for adjusting anti-diabetic medications
  1. Unsatisfactory treatment outcomes: according to FBG results, or 2-hour postprandial blood glucose, or HbA1c
  2. Adverse events: hypoglycemia, gastrointestinal reactions, edema, weight gain, change of liver or kidney functions, allergic, other discomforts.
  3. Economical reasons
  4. Self-adjustment: details will be required
- Compliances: does the patient routinely take medicines in accordance with the prescriptions, if not, the specific reasons will be required
- Hypoglycemic symptoms and severity: Hypoglycemia is defined as the fasting plasma glucose level below 70 mg/dL according to the American Diabetes Association 2009 Position Statement [12]. The symptoms of hypoglycemia include but not limited to sweating, hunger, trembling, anxiety, confusion, blurred Vision. A simple questionnaire will be used to record patient reported symptoms and severity.
- Lab tests: Blood tests should be performed after fasting for at least 10 hours.
- Serum glucose: The oxidase method should be used;
- HbA1C: It should be determined by high performance liquid chromatography (HPLC)
- Lipid panel: TC – total cholesterol, LDL-C – low density lipoprotein, TG – triglyceride, HDL-C – high density lipoprotein
- Kidney function: serum creatinine
- Liver function (Gamma-GT, ALT, AST)
- Urine test (urine albumin, creatinine or albumin / urine creatinine ratio)

Notice: Lipid panel and liver function are tested every 6 months, while other lab tests are conducted every 3 months.

If any additional diagnose test is ordered as part of the routine medical course, a copy of the results should be obtained. Any change of medical history, hospitalization, and medication will be specially noted (cause, dosage, outcome, etc). Unsolicited safety reports on products marketed by Bristol Myers Squibb will be collected.

Lab test methods:

- - - All blood samples should be venous blood after at least10-hour fasting;
    - HbA1c should be tested using high performance liquid chromatography (HPLC) method;
    - Fasting blood lipids: total cholesterol, triglycerides, high density lipoprotein, low density lipoprotein;
    - Urinalysis: 24 hours urine, short time urine, or random urine are accepted;
    - Albumin to creatinine ratio: urine (3-4 ml) measured within two hours after collection. Urine albumin is tested using immune turbidimetric method. Urine creatinine is tested using oxidase method.
- In addition to the scheduled follow-up visits of NEW2D and the information collected at each visit, the extra visits of the patients should also be briefly recorded, including the date, the reason (needed prescription, needed treatment), having tested for blood glucose, method of the test and the results if available;
- Adverse events: gastrointestinal reactions, edema, weight gain, change of liver or kidney functions, allergic, other discomforts (details);
- Severe adverse events: for BMS products only.
- Self-evaluated life quality is collected with EQ-5D questionnaire at baseline and last visit[21].

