## Exclusion criteria

- Patients who are currently pregnant or are breast feeding, or plan to get pregnant during the following year;
- Patients who are not willing or not able to return to the same hospital for follow up visits every 3 months for one year after enrollment (e.g. do no reside locally);
- Patients who are participating in another interventional clinical trials;
- Patients who have been on diabetes medications but have no clear information for the drugs used;
- Patients who are not willing to sign informed consent form.

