## Study Flow Chart

| **Procedure** | **Baseline Visit** | **Follow Up Visits (3, 6, 9, and 12 months after baseline visit +/- one month)^g^** |
| --- | --- | --- |
| Inclusion/Exclusion Criteria | X |  |
| Written informed consent form | X |  |
| Demographic Data ^a^ | X |  |
| Diabetes history | X |  |
| Family history | X |  |
| Medical history and co-morbidity ^b^ | X | X |
| Knowledge about T2D | X | X |
| Health behavior ^c^ | X | X |
| Physical Exam^d^ | X | X |
| Medication ^e^ | X | X |
| Hypoglycemic symptoms and severity | X | X |
| Laboratory tests ^f^ | X | X |
| Unsolicited safety report ^h^ | X | X |
| Self-evaluated life quality ^i^ | X | X |

1. Demographic data include age, gender, residential region, educational level, and social-economic status.
2. Including cardiovascular event and other complication occurred as medical history or during follow up.
3. Including smoking history and exercise pattern.
4. Including height, body weight, waist circumference, blood pressure
5. Current and any change of medications since last recorded visit for treatment of type 2 diabetes, diabetic complications, lipid-regulation, and hypertension, including prescription drugs, OTC drugs and Chinese herbal medicines with their names and doses.
6. Laboratory tests include: fasting blood glucose, HbA1c, fasting blood lipid (TC, HDL-C, LDL-C, and TG, tested every 6 months), liver function (every 6 months), kidney function (serum creatinine), and urine analysis (microalbumin/albumin, urine creatinine, or albumin to creatinie ratio).
7. An one month time window is permitted for each follow up visit.
8. Adverse events include gastrointestinal reactions, edema, weight gain, liver and kidney function, allergies, etc.
9. Unsolicited safety reports on products marketed by the BMS will be collected, then reported to health bureau and BMS
10. EQ-5D questionnaire will be applied.

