## Secondary endpoints

The secondary endpoints of this study include the following;

1. The proportions of patients receiving one OAD, two OADs, > two OADs, insulin alone, insulin+one OAD, insulin+two OADs, insulin+>two OADs and by class of OADs at 3, 6, 9, and 12 months;
2. Mean duration of diet & exercise alone (t_4_), initial anti-diabetic treatment (ADT) (t_1_), initial ADT is switched or 2^nd^  ADT is added (t_2_), 2^nd^ ADT is switched or 3^rd^ ADT is added (t_3_) ; (Figure 1 Treatment Pattern Diagram);
3. The proportion of patients reached the therapeutic target of glycemic control by treatment regimen and by OAD class at 3, 6, 9 and 12 months:
4. The correlation between treatment patterns and patient demographics, social-economic status, insurance, medical history, HbA1C level, type of hospital, physician years of practice, etc;
5. Incidence of microvasular diabetic complication: diabetic retinopathy, nephropathy, neuropathy, and macrovascular complications: cardiovascular events, peripheral vascular complications, and stroke, at 3, 6, 9, and 12 months;
6. Were the diabetes related clinical examinations applied such as Fundus examination and diabetic foot screening;
7. Incidence of hypoglycemia associated with various ADTs;
8. Diagnosis pattern: to assess the methods of diagnosis (i.e. routine physical examination, seeing doctors for other diseases, etc), and location of diagnosis, demographic information of the patients and the regions of residence;
9. Quality of life assessment (baseline and the last visit);
10. Resource consumption patterns based on the information collected on the cost of medications, cost of diagnostic test and other relevant [procedure.

Figure 1 Treatment Pattern Diagram

[figure not shown]

T1 = duration between diagnosis and initiation of (single) treatment regime， T2 = duration between initiation of single treatment regime and duple regime， T3 = duration between initiation of duple treatment regime and multiple regime

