# SAMPLE SIZE AND STATISTIC EVALUATION

As this is a descriptive study, there will be no hypothesis testing. The sample size is calculated based upon a desired margin of error for the proportion of subjects reaching the target HbA1c level.

In the 2007 Chinese Guideline for Diabetes Prevention and Treatment [20], the target HbA1c level was set to be <6.5%,. However, in the newest Chinese Guideline published in November 2011 [19], the target HbA1C level has been adjusted to <7.0%, based on the evidence showing that HbA1c<7.0% is already associated with decreased incidence of diabetic complications and that further reduction of HbA1c with using more aggressive intervention might result in an increased incidence of hypoglycemia. In patients with cardiovascular complications, further reduction of HbA1C beyond 7.0% may even be associated with increased risk of CV events. On the other hand, for newly diagnosed patients, the latest guideline still recommended to aim for normal level of HbA1C (<6.5%) by using insulin or other ADT (anti-diabetic treatment) with low risk of hypoglycemia. The target HbA1C level for this study is thus set to be consistent with the guideline, i.e. 6.5%.

According to the results of the Polish ARETAEUS1 study [19], 28.9% of the patients who were diagnosed with T2D within 2 years achieved a therapeutic target of HbA1C <6.5%. Pan et al [14] reported 25.9% of T2D patients in China achieved a target glycemic control level of HbA1C <6.5%. A recently completed CCMR study showed that 30.7% of the stabilized T2D patients (diagnosed more than 6 months) in China reached this therapeutic target. We thus estimate that the proportion of newly T2D patients reaching the target of HbA1c < 6.5% in this study is approximately between 26%-31%.

Assuming a confidence level of 95%, a confidence interval of 0.05 (margin of error of +/- 2.5%), and the expected proportion (p) of 0.30, n=1,315 subjects are required. To ensure each of the three hospital tier has sufficient subjects to demonstrate the assumed proportion of patients reaching the target HbA1c <6.5%, the total sample size would be n=3,945 (1,315 x 3). Attrition is often a challenge in observational studies and three recent, large population-based observational studies of diabetes patients in China reported attrition rates ranging from 14% to 25%. Assuming an attrition rate of approximately 20% for this study, a sample size of 4,931 is required.

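### Secondary endpoint 5 depends on patients returning: the protocol has no vital-status item and no event check for those who stop attending, so fatal and disabling cardiovascular events and strokes are likely to be under-counted.

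*Protocol*

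**What the plan says.** Section 5.2 sets how follow-up data are obtained: "Each patient will return to see the same physicians for follow up visits at 3, 6. 9 and 12 month after the first visit". In the flow chart (section 5.3), complications enter through the medical-history row of the visit columns, with the note "Including cardiovascular event and other complication occurred as medical history or during follow up".

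Secondary endpoint 5 (section 6.2) covers microvascular complications and, on the macrovascular side, "cardiovascular events, peripheral vascular complications, and stroke, at 3, 6, 9, and 12 months".

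On loss, section 7 reports that "three recent, large population-based observational studies of diabetes patients in China reported attrition rates ranging from 14% to 25"%, assumes about 20% for this study, and inflates the sample size to 4,931. Section 4.3 tries to limit loss at entry by excluding "Patients who are not willing or not able to return to the same hospital for follow up visits every 3 months for one year after" enrolment.

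Section 5.2 has some provision for what happens between visits: "Any change of medical history, hospitalization, and medication will be specially noted (cause, dosage, outcome, etc"), and "the extra visits of the patients should also be briefly recorded". The synopsis has a similar notice on changes in condition and hospitalisations between scheduled visits.

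Death is not an item in section 5.2, the flow chart or endpoint 5. It appears in section 10.2, as a seriousness criterion for reactions to a product and as a line in the drug adverse-reaction reporting table, where it must be reported at once.

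**The concern.** The event endpoint and the way of collecting it do not fit together. A patient who has a fatal infarction or a disabling stroke between visits is among those least likely to attend the next one. The protocol describes no step that would tell the site why the patient did not come, and no study field in which death would be recorded. Such a patient can be handled as attrition, indistinguishable from someone who moved away.

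At stake is the incidence of cardiovascular events and stroke, which is both a stated objective (section 3.2, item 4) and a secondary endpoint, and on which section 7 plans to compare subgroups. An analysis plan can choose denominators and censoring rules, but it cannot recover deaths and strokes that were never collected. This is therefore a matter for the protocol and the eCRF.

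**Working it through.** **1. The plan's own figure.** Inputs from section 7: 95% confidence, margin ±2.5%, p = 0.30, three hospital tiers, about 20% attrition.

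- Per tier: n = 1.96² × 0.30 × 0.70 / 0.025² = 1,291, against 1,315 stated (1.8% apart; p = 0.31 gives 1,315). The difference does not matter here.
- Three tiers: 1,315 × 3 = 3,945.
- Attrition: 3,945 / (1 − 0.20) = 4,931.25, matching 4,931.

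Attrition enters the plan only as this inflation. It keeps about 3,945 patients in the analysis, but says nothing about whether those patients represent the ones lost.

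**2. Patients whose 12-month status would be unknown.**

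- At the assumed 20%: 4,931 × 0.20 = 986.
- At the extremes reported by the three other studies: 4,931 × 0.14 = 690 and 4,931 × 0.25 = 1,233.

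**3. Possible effect on incidence.** The protocol gives neither an event rate nor the dropouts' risk, so this is an illustration. Let a be the proportion lost and R the assumed event risk in dropouts relative to retained patients. Suppose no events are seen in dropouts. True incidence relative to that in retained patients is (1 − a) + aR.

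- Completers as denominator: observed/true = 1 / [(1 − a) + aR].
- All enrolled as denominator: observed/true = (1 − a) / [(1 − a) + aR].

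With a = 0.20:

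| R (assumed) | Completers | All enrolled |
| --- | --- | --- |
| 0.5 | 1/0.9 = 1.11 | 0.8/0.9 = 0.89 |
| 1 | 1/1.0 = 1.00 | 0.8/1.0 = 0.80 |
| 2 | 1/1.2 = 0.83 | 0.8/1.2 = 0.67 |
| 3 | 1/1.4 = 0.71 | 0.8/1.4 = 0.57 |

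With completers as denominator and doubled risk, the relative undercount is 1 − 0.83 = 17%. Over 14% to 25% loss it is 12% (1 − 1/1.14) to 20% (1 − 1/1.25).

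**4. Allowing for data before leaving.** Endpoint 5 is read at 3, 6, 9 and 12 months, so dropouts contribute until they go. Assume that they leave half-way on average, have a constant rate, and that their events to that point are seen. At 20% loss and R = 2, the observed rate per person-time is (0.8 + 0.2 × 2 × 0.5) / (0.8 + 0.2 × 0.5) = 1.0/0.9 = 1.11, against a true 1.20. The undercount is about 7%. This version still does not count the events that themselves end attendance.

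**5. Fatal events.** Here equal risk is impossible. A patient who dies before the month-12 visit cannot be a 12-month completer, so every such death falls among the non-completers. It reaches the data only if the site hears of it by some other route and has a place to record it.

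**The case against.** The strongest reply is that the protocol does not rely on scheduled attendance alone. Interval hospitalisations and changes of history are to be noted, and extra visits recorded. A patient who misses month 6 but attends month 9 can still report what happened. The adverse-event duty in section 10.1 is not tied to a visit, and section 10.2 requires deaths to be reported at once. This stands against a reading that events are collected only from patients who come back, or that fatal events are certain to vanish. It does not close the gap, because every route needs the site to learn of the event and no procedure makes that happen once attendance stops. The section 10 routes lead to the regulator and the funder as drug-safety reports, not to endpoint 5.

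A second reply is that direction and size are unproven. That also stands. With completers as denominator there is no bias at equal risk, and overstatement if dropouts have half the risk. A reader might infer a definite and large undercount: 25% loss with a fourfold risk gives 1 − 1/1.75 = 43%. That result comes from the assumed ratio and from treating dropouts as contributing nothing. A reader might also take 14% to 25% as this study's expected loss, but those are other studies' figures and the protocol assumes about 20%.

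Two further inferences lack support. Distortion between hospital tiers would require return rates to differ by tier, and nothing shows that they do. A shortfall in serious adverse events should not be put down mainly to dropout, since the more direct limit is the restriction in section 5.2, "Severe adverse events: for BMS products only", which affects retained patients too.

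Finally, endpoint 5 is one of ten secondary endpoints in a descriptive study whose primary endpoint is HbA1c. That limits the weight of the point but does not remove it.

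**Conclusion.** The point holds as a gap in data collection. Ascertainment of cardiovascular events and stroke depends on the patient returning or on the site otherwise learning of the event. No vital-status item, death field, contact or record check is described for the roughly 20% (986 of 4,931) expected to be lost. Fatal events are likely to be missed and macrovascular incidence is likely understated.

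The direction rests on the reasoning that death, and plausibly disabling stroke, prevent attendance. The size cannot be derived from the documents. The 17% figure assumes 20% loss, doubled risk in dropouts, completers as denominator and no events seen in dropouts, and it falls to about 7% under the half-way person-time assumptions above. The primary endpoint's definition and the sample-size chain are not called into question. The change should be made, but it is not critical to the study's main result.

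**What to change.** In section 5.2 and the flow chart, add that for any patient who misses a visit, and at month 12, existing site staff make one telephone contact with the patient or family or check the hospital's own record. They record vital status, with date and cause of death, and any cardiovascular event, stroke or hospitalisation. Add a field for date and reason of discontinuation, with death as an option. State in endpoint 5 that fatal cardiovascular events and fatal strokes count. The denominator and person-time convention can be left to the SAP.

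The cost is one eCRF page, a consent line permitting the contact, and modest site time for about 1,000 patients at the assumed loss. No treatment or visit schedule changes.

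Separately, reconcile the section 5.2 limit on serious events to the funder's products with secondary objective 7 (section 3.2), which concerns serious events possibly related to anti-diabetes drugs in general.

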| Study Design | Newly diagnosed (within 6 months) type 2 diabetic patient who is visiting tier 3, 2, or one hospital, may be considered for enrollment in this study, as long as the patient meets the inclusion and exclusion criteria and is willing to sign on the informed consent form.  Enrolled patients will receive routine treatment (diet & exercise or medication) and will be asked to return to see the same physicians for follow up visits at 3, 6. 9 and 12 month after the first visit.  Following measurements will be recorded, laboratory reports will be obtained.  Baseline measurement only:   - Demography - Medical history and co-morbidity - Diabetes history and related symptoms - Diabetic complications - Family history - Education level and knowledge about T2D - Social-economic background - Diagnosis methods and information of the health care providers - Questionnaire for diabetes knowledge assessment - Quality of life assessment (repeated at the 12 month visit)   Baseline and follow up visits   - Blood pressure - Health behavior (Smoking history, exercise pattern) - Physical exam (height, body weight, waist circumference) - Medication (including herbal medicine, generic name, brand name, dosage, frequency, years taken, purpose, reason for switch of medication, if necessary) - Hypoglycemic symptoms and severity - Lab tests: - Serum glucose - HbA1c - Lipid panel (Total cholesterol, triglyceride, LDL, HDL) - Kidney function (serum creatinine) - Liver function (Gamma-GT, ALT, AST) - Urine analysis (albumin, creatinine or albumin to creatintine ratio)   If any additional diagnostic test is ordered as part of the routine medical course, a copy of the results should be obtained. Any change of medical history, hospitalization, and medication will be specially noted (cause, dosage, outcome, etc).  Notice:   1. Lipid panel and liver function are tested every 6 months, other lab tests are conducted every 3 months 2. If the patients have extra visits or examinations between any two scheduled visits, the reasons for these visits and the related treatment and test results should be recorded 3. If there are changes of disease conditions, hospitalizations or medications between any two scheduled visits, the related details should be recorded (reasons, dosages, results, *etc*) |

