# STUDY PROCEDURE

## Baseline Measurements

- Demography: Age, gender, residential region.
- Diabetes history and related symptoms: Duration or diagnosis (must be < 6 months), how was diagnosis made (using the 2010 Chinese Guideline for Diabetes Prevention and Treatment [19]) , signs and symptoms.
- Diagnostic pathways:
  1. Seeking health care due to diabetic symptoms
  2. Already found an increased blood glucose once, and confirmed by a second test
  3. Seeking health care due to other diseases
  4. Self-demanded lab tests
  5. Participating in an epidemiological study / campaign
- Screening methods for diabetes (could be singular or multiple choices):
  1. OGTT test
  2. “Bun test”
  3. Urine glucose
  4. Others
- Diagnostic methods for diabetes* (reference table 1), diabetic symptoms plus:
  1. Random blood glucose (the blood glucose level at any time during a day without knowing the time of last meal)
  2. FBG (fasted for at least 8 hours without calories intake)
  3. 2-hour postprandial blood glucose
- Diabetics symptoms: thirsty, constant hunger, frequent micturition, obvious weight loss, fatigue, prone to inflammation, blurred vision, numbness/pain, leg or foot ulcers, skin itching, acute complications such as ketosis, hyperosmolar coma, *etc.*
- The hospitals and departments where diabetes was diagnosed:
  1. Tier 1 hospital
  2. Tier 2 hospital: endocrinology dept., internal medicine dept.
  3. Tier 3 hospital: endocrinology dept., internal medicine dept.
- Disease history:
  1. Diabetic complication history: the acute or chronicle diabetic complications at or after the diagnosis, including ketosis, hyperosmolar coma, HHS, micro blood vessels lesions (retinal lesions, nephrological diseases, peripheral neuropathy).
  2. Medical history and co-morbidity: Including any major medical procedure or surgery occurred within the last 12 months, any major co-morbidity (e.g. cardiovascular disease, renal disease, other diabetic complications, cancer, etc).
- Family history: Family history of diabetes and cardiovascular diseases
- Education level and knowledge about T2D: Highest formal education received as well as response to simple questionnaire assessing the level of knowledge about T2D.
- Social-economic background: Employment status, marital status, monthly income, insurance type and coverage.
- Questionnaire for diabetes knowledge assessment
- Quality of life assessment (repeated at the last visit)

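### Secondary endpoint 2 needs treatment-step durations, but the protocol times drug exposure only in years taken and requires no start, stop or change date

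*Protocol*

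**What the plan says.** **What is collected.** Section 5.2 gives the medication items as "Record generic name, brand name, dosage, frequency, years taken, and purpose". The synopsis (Study Design) repeats the list and ends it with "years taken, purpose, reason for switch of medication, if necessary". The medication note to the Study Flow Chart (5.3) asks for "Current and any change of medications since last recorded visit for treatment of type 2 diabetes", together with names and doses. Section 5.2 adds: "Any change of medical history, hospitalization, and medication will be specially noted (cause, dosage, outcome, etc", with a list that is left open. The synopsis has a similar open list for events between scheduled visits. A date is explicitly required for extra visits, along with the reason for the visit.

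**Who is enrolled.** Diabetes history at baseline (5.1) includes "Duration or diagnosis (must be < 6 months". The exclusion criteria remove treated patients only if the drugs they used are unclear, so patients already on treatment may enter.

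**What is to be estimated.** Secondary endpoint 2 (6.2) is a set of mean durations, t1 to t4. The legend to Figure 1 says "T1 = duration between diagnosis and initiation of (single) treatment regime", and T2 and T3 run from the start of one regimen to the start of the next. T4 is the time on diet and exercise alone.

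**The concern.** The primary objective is how treatment patterns evolve. Secondary endpoint 2 is the listed endpoint that measures the time spent at each step. It is a difference between calendar events: diagnosis, first drug, second drug, third drug. The only exposure-time item that the protocol names is in years, a unit that suits long-standing diabetes but not a cohort less than 6 months from diagnosis.

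If sites record what the protocol lists and no more, the timing of any step before enrolment is never collected. Later visits cannot supply it, because the event precedes baseline, and an analysis plan cannot restore it. After baseline, some steps would be located only between two visits. Two steps in the same interval would lose their sequence, although secondary objective 1 asks about the process of each change.

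**Working it through.** The protocol states no expected value for T1 to T4, so there is no figure to reproduce. The check is how finely the listed items can locate each step.

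**1. Steps before enrolment.** Time since diagnosis is under 6 months (5.1), so exposure to a drug started after diagnosis is under 6/12 = 0.5 year. Truncated or rounded to whole years, every such value is 0, whether treatment began last week or five months ago. The item could separate patients only if entered as a fraction (for example 3/12 = 0.25), which the protocol does not request.

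| Duration | Needs | Listed item | Result in patients treated before entry |
|---|---|---|---|
| T1 | diagnosis, first drug start | time since diagnosis; years taken | start not resolvable |
| T4 | end of diet and exercise alone, i.e. first drug start | years taken | end not resolvable |
| T2 | first and second regimen starts | years taken; change since last visit | origin not resolvable |

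The wording of endpoint 2 can also be read as making t1 the time on the initial drug, unlike the legend. Either reading needs the first drug's start.

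**2. Width of the interval after baseline.** Visits are at 3, 6, 9 and 12 months, each +/- 1 month (5.3).
- Nominal gap: 6 - 3 = 3 months.
- Largest gap: (6 + 1) - (3 - 1) = 5 months.
- Smallest gap: (6 - 1) - (3 + 1) = 1 month.

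**3. One step, start known exactly, change known only to the interval.** The protocol gives no distribution, so exponential waiting times with mean 3, 6 or 9 months are assumed, with visits uniform in their windows and at least 200,000 simulated patients per case. Figures are mean months among changes that occur within follow-up.

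| Assumed mean | True | Previous visit | Midpoint | Next visit | Next visit - true | Midpoint - true |
|---|---|---|---|---|---|---|
| 3 | 2.77 | 1.49 | 3.05 | 4.62 | +1.85 | +0.28 |
| 6 | 4.11 | 2.68 | 4.26 | 5.84 | +1.73 | +0.15 |
| 9 | 4.71 | 3.22 | 4.80 | 6.39 | +1.68 | +0.09 |

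Assigning the change to the next visit adds about 1.7 to 1.9 months. Even a simple midpoint comes within about 0.1 to 0.3 month of the true mean.

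**4. Two steps, both starts after baseline and both moved to the next visit (T2 or T3).** Same assumptions, with exponential mean waits for the first and second step as shown.

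| Mean waits (first/second) | True mean | Recorded mean | Error | Recorded as zero |
|---|---|---|---|---|
| 3/3 | 2.51 | 2.26 | -0.26 | 46% |
| 3/6 | 3.54 | 3.23 | -0.31 | 33% |
| 6/6 | 3.27 | 3.03 | -0.24 | 35% |

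Errors are computed before rounding. The two delays largely cancel in the mean. The cost is that a third to nearly half of these durations become zero, and those pairs have no recorded order or spacing. The simulation treats every change as undated, so it shows the worst case.

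**The case against.** The strongest reply is that the protocol does not say dates are not collected. Patients return to the same physician, so a change prescribed at a visit carries that visit's date. Extra visits are recorded with date and reason, including the need for a prescription. The lists of details for a medication change are open-ended. The Medical Record Worksheet and the eCRF are not shown and may hold date fields. The protocol does not say whole years, and years is a sensible unit for the other concurrent drugs that the same item covers. Finally, endpoints 1 and 3 describe treatment at 3, 6, 9 and 12 months without needing drug dates.

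Most of this stands for the period after baseline. The undated changes would mainly be self-adjustments and changes made elsewhere. A reader might infer that the durations cannot be computed at all. The documents do not support that, because such changes are bracketed by visits and can be analysed as interval-censored. A reader might also infer that T2 and T3 are systematically lengthened. That holds only where the start is known exactly. With both starts moved to visits, the mean is slightly shortened.

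The reply does not reach steps before enrolment. No visit, scheduled or extra, falls on those dates, and an open-ended list is not a requirement. Where the protocol wants a date, as for extra visits, it says so. Nor is this a matter for the analysis plan, since it concerns what is collected.

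**Conclusion.** The point holds in a limited form. The protocol defines a duration endpoint for recently diagnosed patients without requiring the dates on which it depends.

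- **Before enrolment:** T1, T4 and the start of T2 are not resolvable in patients already treated at entry, assuming that sites enter whole years and record nothing beyond the listed items. The protocol gives no figure for the share of such patients; it shows only that they are eligible. It would be wrong to infer from it that they are many.
- **After baseline:** changes not made at a scheduled or dated extra visit are known to within 3 months nominally and 5 at most. Mean durations remain estimable. Under the assumed exponential waits, up to 33% to 46% of two-step durations would be recorded as zero if all changes were undated.
- **Not affected:** the primary endpoint (HbA1c below 7% at one year), the sample size, and the endpoints reported by visit.

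The change is worth making before data collection because the lost information cannot be recovered afterwards. It concerns one secondary endpoint and the sequence of steps in secondary objective 1.

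**What to change.** - In the synopsis medication list and section 5.2, for glucose-lowering drugs, replace years taken with start and stop dates for each drug since diagnosis, including before enrolment. Month and year are acceptable. Keep years taken for other concurrent drugs.
- In section 5.2 and the medication note to the Study Flow Chart, require a date for each switch, addition or stop.
- In section 5.1, record diagnosis as a date.
- In section 6.2, state that T1 to T4 are derived from these dates.

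The cost is two date fields per glucose-lowering drug line, a date for diagnosis, a few protocol sentences and slightly more entry time, partly from asking patients about the months before enrolment. If the eCRF already holds these dates, one sentence aligning the protocol with it is enough.
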